#### Randomisation, blinding and allocation concealment

Following baseline assessment, the participant will be randomised to one of the three trial intervention arms. Randomisation will be performed by an online randomisation system developed and maintained through the Sheffield Clinical Trials Research Unit (CTRU). The randomisation sequence will be generated in advance by the trial statistician. Randomisation will be stratified by centre (as heterogeneity between centres is expected), and according to severity of word retrieval at baseline, based on percentage scores on the Naming Objects subtest of the Comprehensive Aphasia Test (severe = 10 to 34%, moderate = 35 to 64%, and mild = 65 to 90%). The research speech and language therapist will then inform the participant which group they have been allocated to and draw their attention to the description of this group in the information sheet.

#### Blinding

This is a single blind study. The patient participants are not blind to their treatment allocation. The speech and language therapists performing baseline assessments will do this prior to randomisation. A second speech and language therapist at each site, blinded to group allocation, will perform follow-up assessments. The speech and language therapist setting up the treatment will ask participants not to discuss treatment with the person coming to carry out the follow-up measures. It is possible that unblinding will happen during conversation and the speech and language therapists will be asked to record instances of this. A primary outcome is functional communication in conversation. Video recordings of conversations will be presented in random order to speech and language therapists in the project coordinating centre to rate, blind to treatment allocation and follow-up time. The chief investigator, study manager, statisticians and health economist will all be blind to group allocation.

#### Interventions

##### Usual care control arm

Usual care for this pragmatic study may consist of participation in a range of activities to a greater or lesser extent. Usual care varies across the country in terms of type, frequency and length of provision, and is dependent upon available resources in each locality. Findings from the pilot study confirmed that usual care for four months or more following a stroke may include: face-to-face speech and language therapy targeting language impairment (reading, writing, speaking or understanding); therapy focussing on compensatory communication strategies, provision of communication aids or psychological support; attendance at voluntary support groups or informal communication support from family and friends. Usual care will be recorded retrospectively for three months prior to the study and throughout the study on the case report forms for all groups. Those who are randomised to the usual care group will not receive any project specific intervention.

##### Self-managed computerised therapy intervention

A structured intervention is proposed in addition to usual care as tested in the pilot study. The intervention targets word retrieval as it is one of the challenges most frequently experienced by people with aphasia, restricting their communication. The three components of the intervention are as follows:Qualified speech and language therapist assessment, tailoring of exercises and monitoringThe speech and language therapist at each site will tailor computer exercises to the individual using 100 words of personal relevance chosen by the participant. Photographs imaging the 100 words will be selected from those existing in the software, or can be added from a digital camera or from image stores on a computer. The computer software (StepbyStep© by Steps Consulting Ltd, Gloucester, UK) [30] enables the speech and language therapist to select exercises using these words that follow steps in the therapy process that the therapist would take if delivering it face to face. The speech and language therapist bases the selection of exercises on language skills demonstrated in the initial language assessments. The speech and language therapist will provide initial demonstration of the software exercises, check that the individual is able to use the software and monitor the appropriateness of the tailored exercises. This is expected to take only three to four hours, based on the pilot study [13], as the computer intervention is predominantly self-managed by the patient.Regular self-managed practiceThe participant will then be asked to work through the exercises on the computer and be encouraged to practise each day for 20 to 30 minutes. Participants will be given a six-month period to work though the therapy material on the computer and practise using the new vocabulary in their daily lives. As this is a pragmatic trial, those participants who have the software installed on their own computers will not be prevented from continuing to practise if they wish, following the six-month supported intervention time. Any continued use of software beyond the six months will be recorded.Volunteer support to assist with treatment adherence and carry over into daily activityTo enhance treatment adherence, the speech and language therapist will provide training to local volunteers who already have a working relationship with the SLT department or SLT assistants based in the department. They will use the three-hour training programme and instruction book (University of Sheffield, Sheffield, UK) developed and evaluated during the pilot study. The volunteer will be asked to visit the participant once a month for an hour, or every two weeks for half an hour (to suit the patient), carrying out the following tasks: provide technical assistance; observe and encourage use of computer exercises; check results and discuss difficulties; assist the participant to move on to harder tasks in the therapy process pre-programmed by the speech and language therapist; encourage the use of new words in everyday situations, conversation and discussions with family about how to encourage use and encourage re-use of completed exercises over time.The participants will be able to contact the volunteer or SLTA by telephone for technical advice on computer use between planned visits if necessary. Volunteers and SLTAs will be asked to complete a feedback form on each face-to-face session with a participant and send it to the therapist to enable them to provide tailored advice and support. They therapists are also encouraged to meet with all the volunteers/SLTAs together every two months for support and discussion of issues arising.The majority of the practice time involved in the intervention is self-managed by the participant through regular use of the aphasia computer software. The therapists, SLTAs and volunteers will be asked to keep diaries of resource use showing direct and indirect (telephone and computer set up) time spent and therapist grade (see Table 1).

##### Attention and activity control arm

The third group in this study intends to control for the potential impact of elements of the intervention which of themselves do not provide or require specific speech and language intervention.

Participants randomised to this arm will be provided with generalised activities to carry out and general attention in addition to usual care. On allocation to this group, the speech and language therapists conducting baseline assessments will provide books of standard puzzles that can be purchased from most supermarkets or high street shops. Each book will contain enough activities for one to be carried out each day for at least a month. Examples of puzzles include getting through a maze, spotting the difference between pictures, matching objects that are the same, word searches, Sudoku and so forth. The SLT will provide age appropriate puzzle books that match the participant’s linguistic ability as indicated by the baseline assessments. Puzzle books will be colour coded into levels of easy, medium and hard by the clinicians on the research team centrally and a leaflet will be provided to give speech and language therapists guidance on skills required for each level.

A member of the research team will contact the participants or their carer by telephone or email (whichever is preferred by the participant) once a month to provide the attention similar to that given by volunteers in the intervention arm. They will ask if they are enjoying the activities, how many they have managed to do, whether they would like a new puzzle book sent to them for the coming month and whether they would like the same level of difficulty or an easier or harder one. The participants will also have access to these contact details to enable them to ask for easier or harder books at any time if necessary, again, mimicking the access to the volunteers and SLTAs and type of attention available in the intervention arm.

#### Treatment fidelity

The speech and language therapists delivering this intervention will receive training on how to set up appropriate exercise steps. To enable monitoring of the treatment fidelity, they will be asked to complete a checklist which guides their selection of exercises based on the participant language profile identified during assessment. These will be reviewed centrally by the study quality monitor. Encrypted and anonymised key files from the participants’ software will be returned to the study team to enable comparison of a random selection of exercises provided with the corresponding checklist completed.

As this is a self-managed intervention, adherence of the participants in using the intervention as intended will be monitored. This will be achieved through volunteer or assistant visits with reminders to practise daily and assistance with using the full range of exercises set. The speech and language therapist will also monitor practice through feedback forms provided by the volunteer or assistant. In addition, the software key files returned to the study coordinating team centrally will be reviewed for total practice time and patterns of practice over the six-month treatment period. Practice with the computer for a minimum of 20 minutes three times a week at home on average will be considered per protocol to account for periods of illness and holiday. Volunteer and assistant adherence will be monitored through their feedback forms to the speech and language therapists who will record amounts of support provided. A minimum of four hours in total per patient will be considered per protocol. Adherence to the attention control group will be monitored by recording information regarding the number of puzzles completed and the frequency and duration of telephone support calls received. Usual care will be recorded across the study period for all groups.

#### Data and statistical analysis

##### Sample size

The study aims to recruit 285 participants across 20 speech and language therapy departments (study sites and centres). The sample size of 285 patients in total (95 per arm) is the maximum sample size estimate across the two primary endpoints (word finding ability and functional conversation ability) and key secondary endpoint (patient perception of communication ability) for 90% power and a two-sided significance level of 5%.

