##### Assumptions for the sample size calculation

For improvement in word retrieval the estimated effect size is 10%, with a standard deviation (SD) of 17.38%, from an analysis of covariance (based on results of the pilot study [13]). For assessment of conversation the estimated effect size is 0.45 of a SD (with a correlation between baseline and outcome of 0.5 previously observed in the ACT NoW study). For patient-rated improvement using the COAST questionnaire the estimated effect size is 7.2, with a standard deviation (SD) of 13.5 (with an assumed correlation between baseline and outcome of 0.5). The observed dropout rate was 5 out of 33 (15%; 95% CI: 5 to 32%) in the pilot study, which translated to a completion rate of 28/33 (85%; 95% CI: 68 to 95%) [31].

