### Statistical analysis

Patients with at least one post-randomisation observation will be included in the analysis. Missing data will be described using summary statistics. Data will be checked and cleaned blind to the actual treatment allocation. Data checking will be conducted throughout the study and prior to any analysis of the data.

Primary and key secondary endpoints for the comparisons of control to intervention and active control to intervention will be analysed using a Hochberg testing procedure, which allows for an investigation of all three endpoints whilst maintaining the overall type I error at 5% [32]. This approach has the advantage of not inflating the sample size while maintaining the type I error rate at 5%.

Significance will be declared for the comparison of usual care to intervention if and only if both primary outcomes, word retrieval and conversation, are significant at the 5% level, or if either comparison is significant at 2.5%. If and only if significance is declared for both primary outcomes, a similar comparison of attention control to intervention will be made. Significance will be declared for the comparison of attention control to intervention if and only if both word retrieval and conversation are significant at the 5% level, or if either comparison is significant at 2.5%.

If and only if significance is declared for the comparison of attention control to intervention for both comparisons will the key secondary outcome measure (patient perception of communication and related quality of life, measured using the COAST rating scale) be used in a further comparison of usual care to intervention. If and only if this comparison is significant at the 5% level will the intervention be compared to attention control based on the COAST questionnaire (see Figure 2).

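### The 90% power stated for COAST is a single-comparison figure; under the plan's own gates COAST has about 76–79% against usual care, and no endpoint correlation lifts it to 90%

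*Protocol article*

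**What the plan says.** The Sample size section of the protocol article states: "The sample size of 285 patients in total (95 per arm) is the maximum sample size estimate across the two primary endpoints", and it then extends this to the "key secondary endpoint (patient perception of communication ability) for 90% power and a two-sided significance level of 5"%. So one power figure covers word retrieval, conversation and COAST alike.

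Statistical analysis sets out a sequence:

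1. Both primaries are tested against usual care by Hochberg. The step is declared if both reach 5% or either reaches 2.5%.
2. "If and only if significance is declared for both primary outcomes, a similar comparison of attention control to intervention will be made". The same declaration rule then applies.
3. COAST against usual care opens only if significance is declared for both primaries against attention control.
4. COAST against attention control opens only if step 3 succeeds at 5%.

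Of this procedure the article says: "This approach has the advantage of not inflating the sample size while maintaining the type I error rate at 5"%. It gives no power for any gated step, no effect size specific to attention control and no correlation between endpoints.

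**The concern.** COAST never has a free-standing 5% test. Four primary comparisons must succeed before it is examined at all, so the probability of declaring it cannot exceed the probability that its gate opens. Listing it among endpoints sized for 90% power attaches a figure to COAST that the sequence cannot deliver.

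The attention-control step has a milder form of the problem. It is reached only after both primaries win against usual care, and it is sized with the effects assumed in general. Yet that arm is included because attention and activity might themselves have some effect.

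What is at stake is interpretation. The Discussion describes the trial as fully powered. If COAST is not reached or not significant, a reader relying on the Sample size section would credit the design with more sensitivity than it has.

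**Working it through.** **Inputs** (Assumptions for the sample size calculation)

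- Words: "For improvement in word retrieval the estimated effect size is 10%, with a standard deviation (SD) of 17.38%, from an analysis of covariance". The SD is taken as a residual SD.
- Conversation: "For assessment of conversation the estimated effect size is 0.45 of a SD (with a correlation between baseline and outcome of 0.5").
- COAST: "the estimated effect size is 7.2, with a standard deviation (SD) of 13.5 (with an assumed correlation between baseline and outcome of 0.5").
- Dropout 15%, so 95 × 0.85 = 80.75 completers per arm.

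**Standardised effects on the residual scale**, dividing by √(1 − r²) = √0.75 = 0.866 where a baseline correlation is given:

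- Words: 10/17.38 = 0.575
- Conversation: 0.45/0.866 = 0.520
- COAST: (7.2/13.5)/0.866 = 0.616

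**Reproducing the plan's figure.** Per arm, n = 2(1.960 + 1.282)²/δ². This gives 64, 78 and 56 (65, 79 and 57 with the t distribution). Dividing the t values by 0.85 gives 76.5, 92.9 and 67.1. Conversation sets the size at about 93 per arm, or 279 in all, within about 2% of the stated 285. The sample size therefore stands as the maximum of three single-comparison calculations.

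**Single-comparison power at 80.75 per arm.** Power ≈ Φ(δ√(80.75/2) − 1.960), with √40.375 = 6.354:

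- Words: Φ(3.656 − 1.960), about 95%
- Conversation: Φ(3.302 − 1.960), about 91%
- COAST: Φ(3.913 − 1.960), about 97%

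**Power under the sequence.** I simulated normal test statistics for three arms sharing the intervention arm, with the gates as written. Assumptions not in the article: endpoint correlation 0 to 0.5, and the effect against attention control either equal to that against usual care or 75% of it (attention alone giving a quarter).

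| Event | Equal effects | Attention gives a quarter |
|---|---|---|
| Step 1 declared by its own rule | 97–99% | same |
| Both primaries win vs usual care (gate to step 2) | 87–88% | same |
| That gate passed and step 2 declared by its own rule | about 86% | 74–79% |
| Both primaries win vs both controls (gate to COAST) | 78–80% | 51–57% |
| COAST declared vs usual care | 76–79% | 50–57% |
| COAST declared vs both controls | 74–79% | 42–53% |

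Under Hochberg against usual care, each primary keeps its power: words 94–95% and conversation 90–91%, for correlations of 0 to 0.7.

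**Sensitivity, equal effects.** At correlation 0.7, step 1 has about 96% and COAST about 81%. If the COAST SD of 13.5 is not reduced for the baseline correlation, COAST falls to 71–77% against usual care and 67–74% against both controls (correlation 0 to 0.5).

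**Ceiling for COAST.** Its gate needs conversation to reach 5% against both controls. Each of those tests has about 91% power, and because they share the intervention arm their statistics correlate at 0.5. The chance that both succeed is about 85%, whatever the correlation between endpoints. COAST cannot exceed that, however large its own effect. Simulation at near-perfect endpoint correlation agrees, at about 85%.

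**The case against.** The strongest reply is that Sample size openly describes a maximum over per-endpoint calculations, claims nothing about the sequence, and is arithmetically sound. That stands: a reader might infer that 285 was miscalculated, and it was not.

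A reader might also take 87–88% as showing the primaries to be underpowered. It does not. That figure is for winning both, which opens step 2. Step 1 also accepts either primary at 2.5%, and each primary keeps at least about 90% under Hochberg. Likewise 78–80% is not the power of the attention-control step. It is the gate to COAST; the step's own rule gives about 86% under equal effects.

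The sentence about not inflating the sample size is defensible as a statement about required n, since the procedure avoids splitting alpha over every comparison. It needs qualifying, not deleting.

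If each gate were read as needing only a declaration by the both-or-either rule, COAST against usual care would have about 92–96%. The wording requires significance for both primary outcomes and later for both comparisons, which favours the stricter reading.

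Finally, the endpoint correlation and the quarter-effect scenario are not in the article, and sequence power may be left to a fuller document. That limits how firmly the ranges can be stated. It does not rescue the 90% attached to COAST, because the 85% ceiling needs no endpoint correlation and any smaller effect against attention control lowers it.

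**Conclusion.** The point holds for the gated tests. The 90% figure is valid for each endpoint in one comparison with usual care, and for each primary under Hochberg against usual care. It is not valid for COAST as the plan tests it: about 76–79% against usual care and 74–79% against both controls, with a ceiling near 85%. Passing the first gate and declaring the attention-control step has about 86%, a modest shortfall under equal effects that widens to about 74–79% if attention alone yields a quarter of the benefit.

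These figures rest on 15% dropout, the article's effect sizes, the strict reading of the gates and, except for the ceiling, an assumed endpoint correlation of 0 to 0.5. The documents do not support the broader inference that the trial is underpowered for its primary comparison.

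**What to change.** Keep 285 and the testing sequence. In the protocol article:

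- In Sample size, say that at least 90% is the power of each endpoint in a single comparison with usual care at two-sided 5%.
- Take COAST out of the unqualified 90% statement and give its power under the sequence.
- For the attention-control step, give two figures: power by its declaration rule and power for winning both primaries. State the assumed endpoint correlation and the assumed effect against attention control, with a row for a smaller effect.
- In Statistical analysis, qualify the remark about sample size by adding that the gates lower the power of the later tests.

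The cost is wording and a less favourable stated figure. No test, threshold or recruitment target changes.

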##### Assumptions for the sample size calculation

For improvement in word retrieval the estimated effect size is 10%, with a standard deviation (SD) of 17.38%, from an analysis of covariance (based on results of the pilot study [13]). For assessment of conversation the estimated effect size is 0.45 of a SD (with a correlation between baseline and outcome of 0.5 previously observed in the ACT NoW study). For patient-rated improvement using the COAST questionnaire the estimated effect size is 7.2, with a standard deviation (SD) of 13.5 (with an assumed correlation between baseline and outcome of 0.5). The observed dropout rate was 5 out of 33 (15%; 95% CI: 5 to 32%) in the pilot study, which translated to a completion rate of 28/33 (85%; 95% CI: 68 to 95%) [31].

### Internal pilot

The initial phase of the study will be conducted as an internal pilot trial and will include clear criteria to inform decisions about progression. Data from the internal pilot will be included in the final analysis. The internal pilot trial will be limited to six sites (over 25% of the total), representative of the sites which will be in the substantive study. However, during this phase we will recruit and commence set-up processes for all the intended sites. The progression criteria will be reviewed eight months from site set-up of the sixth site in the internal pilot trial. We are estimating that this will be approximately halfway through the recruitment phase, at 22 months from contract start.

The progression will be based on achieving the following criteria: recruitment of no fewer than 30 participants (10% of the target for the full trial), a minimum participant retention rate of 65%, 80% of participants having been offered a volunteer and 70% of participants continuing to be supported by the same volunteer for their six-month treatment period.

